#### Economic evaluation

The economic analysis will include costs to health and social care service providers and health benefits to patients. The time horizon for the evaluation is 12 weeks as per the scheduled trial follow-up. As such neither costs nor outcomes will be discounted. The data will be analysed on an intent-to-treat basis.

The measure of health benefit for the primary economic analysis will be quality adjusted life years (QALYs). This will be estimated from the EQ-5D-3 L and associated utility tariffs. Secondary analysis will explore the cost-effectiveness of arthritis gloves using the primary clinical outcome measure, change in hand pain during moderate activity between baseline and follow-up. The direct costs of healthcare resources used during the trial will be estimated by combining the level of use reported by participants with the unit cost specific to that resource. The unit costs will be derived from published national average unit cost data, the price year will be 2016. Total direct costs will also include the cost of the gloves. Regression analysis will be used to estimate the net total costs and economic benefits of the arthritis gloves compared to the placebo gloves, adjusting for baseline values and the stratification variable (recent DMARD changes).

Cost-effectiveness will be measured as an incremental cost-effectiveness ratio (ICER) for the arthritis gloves versus the placebo gloves. As recommended by NICE for health technology appraisals [34], cost-effectiveness acceptability analysis will be conducted. Non-parametric bootstrapping of the incremental costs and outcomes (estimated from the regression analysis) will be used to estimate the probability that arthritis gloves are cost-effective compared to placebo gloves.

### Data monitoring

The trial will not have a separate Data Monitoring Committee (DMC), as the safety risks associated with this study are very low. Consequently, there are no stopping rules for safety. The project will be overseen by a Trial Steering Committee (TSC), which will perform this function.

### Harms

There is minimal risk or discomfort associated with the intervention (Isotoner) gloves. If a participant has increased hand swelling due to an exacerbation of their condition after glove provision, this can affect fit and potentially cause tingling or numbness. The verbal and written instructions provided during glove provision emphasise that the participant should: regularly check their hands; not wear the gloves continually; stop wearing the gloves if they experience any discomfort or pain or there is any redness or skin reaction; and contact the occupational therapist if they experience any problems.

Glove use will be modified or discontinued by the treating occupational therapist only if an adverse event related to glove wear causes concern. This may occur at the review appointment or if the participant contacts the occupational therapist with concerns. Adverse events caused by arthritis gloves have been identified in clinical practice and therapists modify the wear regimen as applicable. Adverse events and modifications include:Numbness; pins and needles; and/or fingertips becoming discoloured (i.e. they go red, white or blue) during glove wear. This may be due to gloves being too tight. A larger glove may be fitted if this occurs.Allergic reaction or skin irritation can occasionally occur. Gloves are either left off for a time and re-tried or discontinued.Sleep disturbance at night. This can occur because the gloves feel hot or itchy. Participants are recommended to wear the gloves for part of the night or leave them off when necessary.

It is unlikely any harm will arise from participants wearing placebo gloves as most adverse events occur due to pressure effects.

Any adverse event considered by the occupational therapist to be resulting from glove wear, or any other minor problems related to glove wear, will be recorded by the occupational therapist on the A-Gloves Occupational Therapy Treatment Record Form at the review appointment and a copy returned to the CTU Data Manager.

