#### Adherence

Recommendations for when to wear gloves will be based on individual needs; most, but not all, patients will be provided with gloves for both hands. Most people experience hand pain during the day and are recommended to wear gloves during activity. Those experiencing hand pain at night, which interferes with sleep, will also be recommended to wear gloves at night. Gloves are not recommended to be worn continually. All participants will receive written information about glove wear and care, using the sample information sheet in the A-Gloves Occupational Therapy Glove Provision Manual [17].

To check for correct glove fit and any problems, occupational therapists will either: within two to four weeks of glove provision offer a review appointment (in person or by telephone); or ask the participant to get in contact if experiencing problems, if this is their normal departmental policy. At the review appointment, participants will be reminded about their glove wear regimen and the need to continue to wear the gloves until the 12-week follow-up questionnaire is completed. At the end of their trial participation, they will be contacted with further instructions about future glove wear.

Adherence to glove wear will be assessed in the 12-week follow-up questionnaires, by asking participants to describe their glove wear for right and left hand gloves. This will include, over the last four weeks, the: average time worn during the day and/or at night; and the average number of days per week gloves were worn. The participant will also be asked to state whether they have obtained arthritis gloves from elsewhere (if they did so, as it is possible for patients to purchase gloves in shops and on-line) and glove wear related to these (if applicable).

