	If yes, what type these were			✓
	How their hands are in comparison to 12 weeks ago, i.e. before receiving gloves	(much better/better/no change/worse/much worse)		✓
	Concurrent use of any resting, wrist, finger or thumb splints			✓
	Adherence to glove wear	During the day and at night for right/left hand gloves; average time worn at night/during the day; average number of days per week gloves have been worn		✓
	Whether participants considered gloves provided any benefit	Yes/No		✓
	Whether they will continue to wear the gloves provided	Yes/No		✓
	If they considered the gloves of any benefit, what were these			✓
	Any problems encountered when wearing gloves	Freetext		✓

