### Participant timeline

Participants will complete a baseline questionnaire following consent and prior to the randomisation at week zero. Within three weeks of randomisation, an occupational therapy glove fitting appointment will be arranged to ensure there is sufficient length of time to wear the gloves prior to the 12-week follow-up. Two to four weeks after glove fitting (dependent on each departments’ usual practice), participants will attend an occupational therapy review appointment, either in person or by telephone, as per departmental policy. Participants will receive the follow-up questionnaire at 12-week following the date of baseline questionnaire completion. (See Figs. 1 and 2).

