### Blinding

Due to the nature of the intervention it will not be possible for therapists to be blinded to group allocation. As most sites will only have one Rheumatology occupational therapist, both intervention and placebo gloves will commonly be provided by the same occupational therapist. During the glove training and site monitoring visits, the importance will be emphasised of not divulging to the participant whether they are receiving an intervention (arthritis glove) or a placebo glove. Therapists will be asked not to use the term “compression” glove (an alternative name for arthritis gloves in clinical practice) in any participant interaction, as this may unblind patients as to whether they are receiving an intervention or placebo glove. Participants will be kept blinded to group allocation by describing the study throughout as a comparison of two types of arthritis glove and not divulging the differences between these.

The trial manager will remain blinded to group allocation until the participant has completed and returned their 12-week questionnaire and the data been verified at the CTU. The trial manager will then be unblinded to group allocation for some participants in order to complete interviews with participants (*n* = 24–30).

Data co-ordination and data entry staff at the CTU, responsible for baseline and 12 weeks questionnaires management, will be blinded to group allocation. However, data entry for the Treatment Records (which identify the group allocation) will be conducted separately by the CTU Trial Management Team only, to avoid other CTU staff becoming unblinded. Statisticians and the health economist will be blinded to group allocation until analysis is complete.

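### Therapist-recorded glove harms are at risk of incomplete and differential ascertainment, and the blinded 12-week item that could offset this is not named for reporting

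*Protocol article*

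**What the plan says.** **Therapist form.** The Harms section of the protocol article has the therapist record "Any adverse event considered by the occupational therapist to be resulting from glove wear". Lesser difficulties are noted too, provided they are linked to the gloves. The place and time of recording are given as the "Treatment Record Form at the review appointment and a copy returned to the CTU Data Manager".

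**Blinding.** The Blinding section states that "it will not be possible for therapists to be blinded to group allocation". It adds that the same therapist will commonly fit both glove types, and that participants are kept blinded.

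**The review.** The Adherence section offers two routes: a review in person or by telephone 2 to 4 weeks after glove provision, "or ask the participant to get in contact if experiencing problems, if this is their normal departmental policy". The Participant timeline gives one route: "participants will attend an occupational therapy review appointment, either in person or by telephone, as per departmental policy".

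**Self-report.** Table 1 includes a 12-week free-text item, "Any problems encountered when wearing gloves", and the Abstract confirms that the follow-up questionnaire asks about problems. In Data collection methods, the data set obtained by telephone from people who do not return the questionnaire does not include this item, either in its minimum content or among its optional extras.

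**Reporting.** Statistical methods lists the descriptive data to be reported: medication use, other treatments, perceived benefit, continued use, adherence and the therapist treatment record. Problems with gloves are not on the list.

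**The concern.** Both routes onto the therapist form require someone who knows the allocation to judge that the glove was responsible. The Harms section itself expects little harm from placebo gloves, on the ground that most events come from pressure. Yet its own list of known events includes skin irritation and sleep disturbed by heat or itching. These need no pressure, and the placebo glove is meant to give similar warmth. The same complaint could plausibly arise in either arm and be attributed differently.

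The form also has only one stated recording time, and some departments may not schedule that appointment. The Harms section foresees participants contacting the therapist at other times but states no recording step for those contacts.

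The Abstract's Discussion says the results will help services and patients judge the value of gloves, and whether to go on supplying them. Tolerability is part of that judgement. The primary pain outcome is not affected.

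**Working it through.** The plan states no figure for harms, so there is none to reproduce. The check compares the statements with each other and then shows what could and could not separate the arms.

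**1. The two harms sources side by side**

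| | Therapist form | 12-week item |
|---|---|---|
| Who reports | Therapist, unblinded | Participant, blinded |
| Attribution needed | Yes, by the therapist | No therapist judgement |
| When | At the review | Once, looking back |
| Who is covered | Those who have a review | Those who return the questionnaire |
| Named for reporting | Yes | No |

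The source named for reporting is the one filtered by unblinded judgement.

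**2. Is there always a review?** Adherence says either a review or contact if there are problems, by departmental policy. Participant timeline says participants will attend, with policy deciding the format and usual practice the timing. Under the first, some participants have no scheduled recording point; under the second, all have one. Both cannot describe the same procedure.

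**3. Wear after the form's stated recording time.** Data collection methods says most participants will have worn gloves for about 9 weeks at follow-up. With a review at 2 to 4 weeks:

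- review at 4 weeks: 9 − 4 = 5 weeks remain
- review at 2 weeks: 9 − 2 = 7 weeks remain

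About 5 to 7 weeks of wear therefore fall after that point. This concerns the form alone.

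**4. Can missed reviews separate the arms?** Let q be the share of participants without a scheduled review and c the fraction of problems still recorded for them, taking full capture where a review is held. Then

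fraction recorded = (1 − q) + q × c.

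Both inputs are assumptions. With q = 0.10 and c = 0.5 the result is 0.90 + 0.05 = 0.95. With q = 0.50 and c = 0.2 it is 0.50 + 0.10 = 0.60. Review policy belongs to the department, while allocation is by individual, so q should be similar in both arms. If c is also the same, the factor cancels from the ratio of recorded rates. Missed reviews would lower both rates without creating a relative difference.

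**5. Can attribution separate the arms?** With true event rate p in both arms and attribution probabilities a₁ (intervention) and a₀ (placebo),

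recorded ratio = (p × a₁) / (p × a₀) = a₁ / a₀.

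For illustration, assume p = 20% and a₁ = 0.9, so that the intervention arm records 0.20 × 0.9 = 18%:

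| a₀ | Placebo recorded | Ratio |
|---|---|---|
| 0.9 | 18% | 18/18 = 1.0 |
| 0.7 | 14% | 18/14 = 1.3 |
| 0.5 | 10% | 18/10 = 1.8 |

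If therapists attributed more readily under placebo, the ratio would fall below 1. None of these rates is in the documents. The table shows the mechanism and does not estimate its size.

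**The case against.** The strongest reply is that harms are also collected independently of the therapist. The 12-week item is completed by blinded participants in both arms, looks back over the wear period, and needs neither a review nor a therapist's judgement. The form itself takes minor glove-related problems as well as adverse events, and every participant is told to contact the therapist about problems. The Auditing section provides for central monitoring of adverse event reporting. No between-arm harms test is among the objectives. The full analysis plan, the form and the glove provision manual are not shown and may settle how the data are logged and presented. The gloves are described as very low risk.

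Much of this stands, and it rules out several stronger readings that a reader might infer:

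- **That harms are recorded only through the therapist.** Table 1 and the Abstract show otherwise.
- **That at best 4/9 = 44% of wear is covered.** This describes one form's scheduled time point, not harms capture as a whole.
- **That therapists are told placebo harm is unlikely.** The article states that expectation but does not say it is part of their training.
- **That missed reviews will bias the comparison.** They should affect both arms alike.

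The reply does not remove the rest. Minor problems on the form must still be glove-related. The self-report item is unprompted free text, is lost for participants followed up only by telephone, and is absent from an explicit list of data to be reported. The statements about the review still disagree.

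**Conclusion.** The point holds as a risk to one data source. Therapist-recorded harms may be incomplete because their only stated recording time is a review that some departments may replace. They may also differ between arms because an unblinded therapist decides what counts as glove-related. Any differential would come from that attribution, not from missed reviews.

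Neither the size nor the direction can be computed: the documents give no event rate, no attribution rate and no number of departments without a scheduled review. It would be wrong to conclude that harms will be undercounted or will differ between arms; under equal attribution the recorded ratio is 1.0. The conclusion assumes that the form is used as the Harms section describes, and that the list in Statistical methods reflects what will be reported. It is worth correcting because a blinded source is already in the questionnaire and needs only modest changes.

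**What to change.** 1. In the 12-week questionnaire, add yes/no boxes to the glove-problems item for the events the Harms section already names (numbness, pins and needles, fingertip discolouration, allergic or skin reaction, sleep disturbance), and keep the free text.
2. Add the item to the telephone minimal data set.
3. Name it in Statistical methods and report it by arm as the main harms comparison.
4. Have therapists log every problem reported to them, at a review or on contact, whether or not they attribute it to the gloves. Present this as supportive data.
5. Reconcile Adherence, Participant timeline and Harms on whether a review is held. Which arrangement is right is for the trial team to decide.

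The cost is five tick boxes, a slightly longer questionnaire and telephone call, and some wording. No extra visits or staff are needed.

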### Auditing

The trial manager will conduct at least one on-site monitoring visit per year over the course of the study to all clinical sites to educate, support and solve problems. The trial manager will provide the research facilitator/principal investigator with a site file checklist prior to the visit and ask them to ensure the site file is up-to-date. The trial manager will check the completed checklist and site file at the visit. There will also be central monitoring, by the CTU and trial manager, of quality of source documentation, including consent form completion and adverse event reporting.

The Chief Investigator will permit study-related monitoring, audits and inspections by the Ethics Committee, lead R&D department, the University and any NHS Trust Research Governance Managers requiring this. The study will be monitored in accordance with NHS and University Research Governance procedures. The Chief Investigator will ensure that any regulatory authority is given access to all study related documents and study related facilities. Principal investigators will be asked to audit their site files at the beginning and end of the study using a checklist provided by the University Research Centre and to allow study related monitoring, audits and inspections as above.


### Protocol amendments

Any subsequent modifications to the protocol which may impact on the conduct of the study, potential benefit to the patient or may affect patient safety (including changes of study objectives, study design, patient population, sample sizes, study procedures, or significant administrative aspects) will require a formal amendment to the protocol. Such amendment will be agreed by TMG and TSC members and approved by the approving NRES Ethics Committee prior to implementation and notified to the participating Trust R&D departments in accordance with local regulations.

Administrative changes of the protocol are minor corrections and/or clarifications that have no effect on the way the study is to be conducted. These administrative changes will be agreed upon by TMG members and documented in a Memorandum filed in the trial master file. The approving NRES Ethics Committee may be notified of administrative changes at the discretion of the TMG. Protocols and documents will be version controlled.

### Dissemination

Findings will be submitted to rheumatology and health professional conferences and journals. A summary of findings will be provided to relevant health professional and arthritis patient organizations, requesting these are included in websites and newsletters. We will also produce guidelines, for both therapists and patients, on how to correctly fit and wear arthritis gloves, based on the A-GLOVES Trial Occupational Therapy Glove Provision Manual [17] and disseminate these as above.

## Discussion

This protocol describes a definitive, pragmatic, patient-blinded, and multi-centre superiority randomised parallel group trial, which aims to determine the effectiveness and cost-effectiveness of the use of arthritis gloves for people with RA or IA with persistent hand pain. The results of this trial will inform the evidence base to support the prescription of arthritis gloves for people with RA or IA and hand pain. The results of this study will be published as soon as they become available.
